### Cost-effectiveness

We will use registry data: NPR (*Norsk Patientregister*), KPR (*Kommunalt pasient- og brukerregister*), and KUHR (*Kontroll og utbetaling av helserefusjoner*), to estimate hospital and community health care and social care resource use from three months prior to baseline measurement and 3, 6, and 12 months after baseline measurement. To support the economic evaluation, our own questionnaires include items of health and social care use in a broader sense than collected registry data. All participants in the study will be assessed with self-reported measures and registry data comprising work-related data and health and social care use.

At baseline, we will collect demographic data and details of health care use in the past 3 months as well as health-related outcomes using the following validated questionnaires, which will be offered in Norwegian or English as preferred: health-related quality of life (EQ-5D-5L) [37, 38], the Warwick-Edinburgh Mental Well-being Scale [34, 39], PROMIS-29 [40, 41], and the Work Ability Score (as a single item taken from the Work Ability Index) [42, 43]. The EQ-5D-5L has been translated into Norwegian using the EuroQul Group translation methodology and Solberg et al. concluded that the instrument is reliable [44, 45]. Garratt et al. compared the EQ-5D-5L to the EQ-5D-3L, which has undergone limited evaluation in Norwegian patients with LBP, to examine floor and ceiling effects, response consistency, and concurrent validity, and found the 5L preferable to the 3L [46]. Garratt et al. have also reported Norwegian population norms for the instrument [47]. Work to determine a Norwegian value set is ongoing and anticipated to be available by the end of the trial [37]. Smith et al. did a confirmatory factor analysis and examined criterion validity and measurement invariance of their Norwegian version of the WEMWBS, reporting that it appears to measure mental well-being well and commending it for use [48]. Garratt et al. reported the Norwegian version of the PROMIS-29 to be a reliable and valid generic self-reported measure of health in the Norwegian general population, having done confirmatory factor analysis to assess structural validity and also examining concurrent validity [49]. The Work Ability Score item in Norwegian to our knowledge has not undergone any formal validation work, which we will acknowledge as a limitation. However, normative data from the Norwegian general population for the question is available for comparison [50].

We will collect follow-up data at 3, 6, and 12 months from baseline measurement, where we additionally will ask about return to work, job offers, or usual care and services, and then, for those who have returned to work: satisfaction with work, the Work Role Functioning Questionnaire (WRFQ) [51, 52], and return to work self-efficacy [53–55] whether work makes the pain worse, healthcare and social care use, medication, and the amount of time they have been at work (Table 1). The WRQF has been cross-culturally adapted into Norwegian using guidelines proposed by Beaton et al. [56, 57]. Johansen et al. examined the internal consistency reporting Cronbach’s alpha coefficients for sub-scales were well-zoned, ranging between 0.80 and 0.90 [57]. The return-to-work self-efficacy scale has been translated into Norwegian and been assessed using principal components analysis, in addition to studies of internal consistency and concurrent validity. Cronbach’s alpha was high enough to indicate the potential for redundant items, although PCA outlined a three-factor structure matching the original instrument. The authors conclude that the instrument has satisfactory cross-cultural validity [55].

In general, there is an absence of work
examining reliability and responsiveness of these instruments, which we will
acknowledge as a limitation.

**Table 1 Tab1:** Outcome domains, measurement instruments, and measurement time points

Domain	Measurement instrument or key items within the questionnaire package	Abbreviation	T0	T1	T2	T3
Demographic	N/A		X			
Pain	Troublesome grid		X			
	Pain duration		X			
Work-related baseline	Educational level		X			
	Unemployed duration		X			
	Looking for work duration		X			
	Reasons for wanting to RTW		X			
Health-related quality of life	Health-related quality of life	EQ-5D-5L	X	X	X	X
	Warwick-Edinburgh Mental Well-being Scale	WEMWBS	X	X	X	X
	Patient Reported Outcome Measurement Information System 29	PROMIS 29	X	X	X	X
	Pain intensity		X	X	X	X
Details of care received and services used	Registry data: Norwegian patient register, Municipal patient and user register, and Control and payment of health reimbursements		X	X	X	X
	Received any care or help for pain last three months* or since the last questionnaire		X*	X	X	X
	List of used medications in last three months* or since the last questionnaire		X*	X	X	X
Work-related	Dimensions of Work Ability		X	X	X	X
	Confidence in RTW		X	X	X	X
	RTW self-evaluation		X	X	X	X
	Job offers			X	X	X
	Return to work			X	X	X
For those who return to work	Satisfaction with work			X	X	X
	Pain interference with work			X	X	X
	Work pattern			X	X	X
	Work-role functioning	WRFQ		X	X	X
Sustained RTW (Primary)	Registry data from the Norwegian Labor and Welfare Administration			X	X	X
Adverse events	Case Report Forms			X	X	X

*Last three months for baseline measurement

### Participant timeline {13}

A participant timeline was created according to the SPIRIT guidance and is presented in Fig. 3 [58]. Following admission to the cohort study, baseline measurement will be completed. After baseline measurement, one in three will be randomly selected to be invited to the intervention (see SPIRIT item 16a). If wishing to join the intervention, the participant will be assigned a case manager who will conduct the initial assessment. The case manager will then match the participant to a suitable work placement in collaboration with Manpower. The participant, case manager, and placement supervisor will agree and sign a return to work plan, and the participant will attend a 2-day work familiarisation session prior to the 6-week placement. Self-reported follow-up questionnaires will be completed by all participants 3, 6, and 12 months after baseline.

**Fig. 3 Fig3:**
[figure not shown]
Participant timeline

### Sample size {14}

The sample size calculation is based on detecting a difference of 20% between the intervention group and the remaining cohort achieving a sustained return to work (1:3 allocation ratio). Assuming a cohort return to work rate as high as 10%, with a power of 80% and a 5% significance level, we will need data on 176 participants (132 control and 44 intervention) [13]. Allowing for a 20% loss to follow-up and a crude 14% inflation in the intervention group for an estimated design effect due to clustering by the case manager (assumptions here are an ICC of 0.01, smallest cluster size of 7 and largest of 16, and so a design effect of 1.14), we will aim to recruit 228 people [59]. If a 1:3 ratio allocation provides insufficient throughput for us to regularly form small groups of people for the work preparation session due to the proportion of people not accepting the intervention being high, we may switch to target overall balanced randomisation (1:2). In this case, our overall required sample size will be reduced to 190 in total, with the above inflations (with the same assumptions the estimated design effect will be 1.11 in this case) [59].

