### Trial design {8}

We will use a single-site cohort randomised approach. The trial will be conducted within a superiority framework. Initially, all eligible and consenting participants will be recruited for an observational cohort study. After baseline measurement, we will randomly select one in three, to whom we will offer the intervention and request consent for intervention participation. Figure 1 illustrates the plan for the delivery of the intervention using a cascade diagram [14]. Assessments will be made at baseline and at 3-, 6-, and 12-month follow-up, and the primary outcome of return to work will be obtained from questionnaire and registry data at these time points. We will also use registry data at all follow-up time points to estimate hospital and community health and social care use for our economic analysis from a personal social services perspective. A pre-pilot informs logistical processes and pre-pilot participants may be included in the main trial if there are no substantial protocol amendments during the pre-pilot, or as a result of piloting (i.e. no alteration in the cohort and intervention delivery). Parallel to the intervention, we will run a process evaluation exploring implementation, continuity of the provided package, reasons for participating and declining participation, and mechanisms behind cases of sustained return to work. The study will be reported following the CONSORT guideline (Consolidated Standards of Reporting Trials; http://www.consort-statement.org/) extension for the reporting of randomised controlled trials conducted using cohorts and routinely collected data (Fig. 2) [15]. The study protocol has been written using the structured protocol template for Standard Protocol Items: Recommendations for Interventional Trials (SPIRIT) Checklist for intervention trials [16].

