### Assignment of interventions: blinding

#### Who will be blinded {17a}

Participants receiving the intervention, study staff directly involved in the trial, and placement providers cannot be blinded due to the nature of the study. It will not be possible to blind the trial statistician to allocation status, due to the nature of sub-sampling 1:3 to be offered the intervention. In the case we switch to 1:2 randomisation, and groups are balanced, the statistician will be blinded.

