### Statistical methods

#### Statistical methods for primary and secondary outcomes {20a}

A detailed statistical analysis plan has been finalised and agreed prior to analysis by the research team. We will report all participant flow in line with the CONSORT guideline extension for reporting RCTs conducted using cohorts and routinely collected data showing withdrawal and loss to follow-up [15]. Analyses will be conducted within TSD using Stata v17 or above (Stata Corporation, College Station, TX). Participant characteristics and outcomes will be summarised as mean and standard deviation for normally distributed continuous data or with median and ranges for data with skewed distributions or counts and percentage for categorical data. The primary analysis approach will be ‘intention-to-treat’. To account for the trial design featuring clustering in the intervention arm, generalised linear (GLM) mixed effects models will be used to estimate the between-group differences for both primary and secondary continuous outcomes, adjusting for age, gender, and duration of pain, with a random intercept for case manager. For example, we will analyse the between-group differences in sustained return to work (a binary outcome) using a generalised mixed-effect model with logit link function, the above covariates, and fitting a random effect in case manager allocation.

Secondary outcomes will also be analysed using generalised mixed models, using link functions appropriate to the outcome (e.g. where outcomes are continuous, we will use a canonical link function). In all cases, we will adjust for the same covariates (i.e. age, gender, and duration of pain). The adjusted treatment effect estimates (mean difference) between the groups will be presented as point estimates within a 95% confidence interval. Our outcome measures are largely independent and no correction for multiple testing will be done. *P*-values < 0.05 will be considered statistically significant. All tests will be two-sided.

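### The sections conflict on the allocation: the design selects one in three, but the sample size (176 analysed, 228 recruited) is calculated at one in four

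*Protocol article*

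**What the plan says.** Trial design {8} reads: "After baseline measurement, we will randomly select one in three, to whom we will offer the intervention". The Methods part of the Abstract, the consent section {26a} and Participant timeline {13} give the same fraction.

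Sample size {14} labels the allocation 1:3 and gives the result as "we will need data on 176 participants (132 control and 44 intervention". It then allows 20% loss to follow-up and a 14% inflation of the intervention group for clustering by case manager, which brings the recruitment target to 228. If too few people accept the intervention to form groups, "we may switch to target overall balanced randomisation (1:2"), with a total of 190 and a design effect of 1.11.

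The blinding section {17a} uses the same notation. The statistician cannot be blinded "due to the nature of sub-sampling 1:3 to be offered the intervention", but would be blinded under 1:2, when the groups are balanced.

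Sequence generation {16a} describes the minimisation but does not give the target fraction, so it does not resolve the question.

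**The concern.** The ratio notation carries two meanings within one paragraph. If 1:2 is balanced, then 1:k means one in k, and 1:3 should mean one in three, as the other sections say. Yet 132 and 44 stand in the proportion three to one, so 44 of 176 is one in four.

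The allocation fraction determines the arm sizes, the recruitment target, the power and what the minimisation script must aim for. A reader cannot tell from the article which fraction is being implemented. If it is one in three, the published arm sizes, total and power belong to a different allocation.

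**Working it through.** **Inputs.** From Sample size {14}: control rate 10%; an effect described as "detecting a difference of 20% between the intervention group and the remaining cohort", read as 10% v 30%; "with a power of 80% and a 5% significance level"; 20% loss; design effect 1.14 in the intervention arm only (1.11 for the balanced fallback). From Statistical methods {20a}: "All tests will be two-sided". The formula is not stated. The one below is inferred because it reproduces all three published totals (176, 228 and 190).

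**Formula.** Fleiss with continuity correction, r controls per intervention participant, p1 = 0.30, p2 = 0.10, d = 0.20, p̄ = (p1 + r·p2)/(1 + r):

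- n′ = [1.96·√((r+1)·p̄(1−p̄)) + 0.8416·√(r·p1(1−p1) + p2(1−p2))]² / (r·d²)
- n = (n′/4)·[1 + √(1 + 2(r+1)/(n′·r·d))]²
- recruited = (controls + intervention × design effect)/0.8

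**Step 1: reproduce the protocol at r = 3.** p̄ = 0.15 and n′ = [1.96·√0.51 + 0.8416·√0.72]²/0.12 = 37.2. With the correction n = 43.6, rounded up to 44, so 44 + 132 = 176. Recruited: (132 + 44 × 1.14)/0.8 = 227.7, or 228. Both match. Without the correction the result is 38 + 114 = 152, which does not match.

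**Step 2: reproduce the fallback.** At r = 1, n′ = 61.6 and n = 71.2, so 72 per arm; (72 + 72 × 1.11)/0.8 = 189.9, or 190. This matches. Reading 1:2 as two controls per intervention participant gives (102 + 51 × 1.11)/0.8 = 198.3, which does not. So 1:2 means one in two.

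**Step 3: one in three, r = 2.** p̄ = 0.1667, n′ = 43.5, n = 50.8, so 51 + 102 = 153 analysed. The protocol gives no design effect for this ratio, so a range is assumed. The lower end, 1.11, is the fallback value. The upper end, 1.18, comes from 76 offers spread over four case managers with all accepted: 1 + (19 − 1) × 0.01.

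| Design effect | Calculation | Recruited |
|---|---|---|
| 1.11 | (102 + 51 × 1.11)/0.8 = 198.3 | 199 |
| 1.14 | (102 + 51 × 1.14)/0.8 = 200.2 | 201 |
| 1.18 | (102 + 51 × 1.18)/0.8 = 202.7 | 203 |

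**Step 4: keep 228 at one in three.** Arms: 228/3 = 76 offered and 152 control. The stated inflations imply 44 × 1.14/0.8 = 62.7, about 63, and 132/0.8 = 165. So 76/63 is about 21% more offers. (63 of 228 is 27.6%, which is neither a quarter nor a third.)

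Power after 20% loss has 152 × 0.8 = 121.6 controls and 76 × 0.8/design effect in the intervention arm:

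| Design effect | Effective intervention n | Power, corrected | Power, uncorrected |
|---|---|---|---|
| 1.11 | 54.8 | 84.7% | 88.9% |
| 1.14 | 53.3 | 84.1% | 88.4% |
| 1.18 | 51.5 | 83.2% | 87.8% |

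For the middle row, the correction is ½(1/53.3 + 1/121.6) = 0.0135 and the standard errors are 0.0604 (null) and 0.0684 (alternative). Then (0.20 − 0.0135 − 1.96 × 0.0604)/0.0684 = 1.00, which gives 84%.

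**The case against.** The best defence is that 1:3 in Sample size {14} means one intervention participant to three controls, and that 132/44 says so plainly. On that reading 176, 228 and 80% are all correct, and one in three is loose wording elsewhere. This stands in part: the arithmetic contains no error, and one in four may have been intended. It does not remove the conflict. Four sections say one in three, and the balanced 1:2 in the same paragraph follows the one-in-k reading.

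A second defence is that the consequence is mild, and this stands. If one in three is used, 228 exceeds the roughly 201 needed. The primary outcome, estimand and analysis model are untouched.

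A reader might go further and infer that placement or case-manager capacity will be too small. The article does not support that:

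- It nowhere says that capacity was planned on 44 intervention participants.
- Its stated worry is too little throughput, and its fallback would put more people in the intervention arm than 76 (72 × 1.11/0.8 is about 100).
- Case managers are assigned only to those who wish to join, and further placement providers may be approached.

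**Conclusion.** The point holds as an inconsistency between sections, not as an arithmetic error. The published 176 and 228 are right for three controls per intervention participant and wrong for the one-in-three selection described in four other places. There the same method needs 153 analysed (51 + 102) and about 201 recruited (199 to 203). Keeping 228 gives 76 offers and 152 controls, with power of about 83 to 85% corrected or 88 to 89% uncorrected.

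A reader might conclude that the trial is underpowered, or that the sample size is simply wrong. Neither follows: the mismatch is conservative if one in three is used, and the article leaves open which fraction was meant.

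These figures assume 10% v 30%, the inferred continuity-corrected formula, 20% loss in both arms and a design effect between 1.11 and 1.18. The upper value assumes four case managers, the top of the planned two to four; fewer managers would raise the design effect under either allocation.

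**What to change.** State one allocation fraction in every section and in the minimisation script.

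- If one in three stands, there are two options. Either restate 153 (102 control, 51 intervention) and about 201 recruited, with the design effect for that ratio. Or keep 228 and restate the expected arms (152 and 76), the design effect and the power.
- If one in four was meant, correct the fraction in the Abstract, Trial design {8}, the consent section {26a} and Participant timeline {13}.
- In either case, write the ratio as control:intervention throughout, so that balanced is 1:1, and correct the notation in Sample size {14} and the blinding section {17a}. Name the formula and the continuity correction so that the figures can be checked.

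The cost is wording, a check that the script targets the stated fraction, and an update of the registration if it repeats the ratio. No participants beyond 228 are needed on these assumptions.

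### The recruitment target of 228 reproduces only as 63 intervention plus 165 control, a split that neither the 1:3 ratio nor one-in-three selection gives

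*Protocol article*

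**What the plan says.** Under Sample size {14} the protocol aims at "detecting a difference of 20% between the intervention group and the remaining cohort achieving a sustained return to work (1:3 allocation ratio"). The control rate enters as "Assuming a cohort return to work rate as high as 10"%, "with a power of 80% and a 5% significance level". Statistical methods {20a} adds that "All tests will be two-sided". From these inputs, "we will need data on 176 participants (132 control and 44 intervention").

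Two allowances follow: 20% for loss to follow-up, and "a crude 14% inflation in the intervention group for an estimated design effect due to clustering by the case manager", with the design effect given as 1.14. The result is "we will aim to recruit 228 people".

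The ratio is described in two ways elsewhere. Who will be blinded {17a} repeats 1:3. The Abstract (Methods), Trial design {8}, the consent section {26a} and Participant timeline {13} say that one in three cohort members is selected for the offer, which is one intervention to two control. Sequence generation {16a} describes minimisation with a two-thirds probability of assignment to the arm that reduces imbalance, and names no target ratio.

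**The concern.** Everyone who completes baseline is randomised. Extra people therefore cannot be added to the intervention arm alone: enlarging that arm requires either a changed ratio or a larger total. The protocol inflates one arm, adds the two arms up, and keeps the original ratio. The total, the ratio and the one-arm inflation cannot then all be true.

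The clustering allowance is meant to protect the smaller arm, which limits precision. At 1:3 most of that allowance goes to the control arm, where it does less good. The power reported with 228 would then differ from the power that 228 gives.

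**Working it through.** **Inputs.** From Sample size {14}: 10% control and 30% intervention (10% plus 20 points), 80% power, 5% significance, 44 and 132 evaluable, 20% loss, design effect 1.14 in the intervention arm only, target 228. From Statistical methods {20a}: two-sided tests. The design effect is taken as given.

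**1. Reproducing 44 and 132.** The protocol names no formula. For two proportions with ratio r = 3, the weighted mean proportion is (0.30 + 3 × 0.10)/4 = 0.15. The uncorrected intervention size is

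n = [1.96 √((1 + 1/3) × 0.15 × 0.85) + 0.8416 √(0.30 × 0.70 + 0.10 × 0.90/3)]² / 0.20² = 37.2.

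The continuity correction gives

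n′ = (n/4) × [1 + √(1 + 2(r + 1)/(n r × 0.20))]² = 43.6, rounded up to 44.

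Three times 44 is 132. This matches the protocol exactly. Without the correction the intervention arm would be 38, so the correction appears to have been used.

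**2. Reproducing 228.**
- Control: 132/0.8 = 165.
- Intervention: 44/0.8 = 55, and 55 × 1.14 = 62.7, rounded up to 63.
- Total: 165 + 63 = 228, an exact match.
- Ratio: 165/63 = 2.62, so 1:2.6.

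**3. What 228 gives at each stated ratio.**
- At 1:3: 228/4 = 57 intervention and 171 control. 57/55 = 1.036, so the arm is 3.6% above the loss-adjusted 55.
- At one in three: 228/3 = 76 intervention and 152 control.

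**4. Power by the same continuity-corrected approximation.** Arms are reduced by 20% for loss, and the intervention arm is then divided by 1.14. With effective sizes nI and nC and mean proportion p̄,

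z = [0.20 − ½(1/nI + 1/nC) − 1.96 √(p̄(1 − p̄)(1/nI + 1/nC))] / √(0.21/nI + 0.09/nC).

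For 57:171, nI = 57 × 0.8/1.14 = 40.0 and nC = 171 × 0.8 = 136.8. Then p̄ = 0.1453, the correction is 0.0162, and the two standard errors are 0.0633 and 0.0769. So z = (0.20 − 0.0162 − 1.96 × 0.0633)/0.0769 = 0.777 (from unrounded values), and power is 78.1%.

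| Recruited (intervention : control) | Effective size | Continuity-corrected | Uncorrected pooled | Fisher exact (sizes rounded) |
|---|---|---|---|---|
| plan's evaluable 44:132 | 44 : 132 | 80.3% | 85.5% | 82.8% |
| 63:165 | 44.2 : 132 | 80.5% | 85.6% | 82.8% |
| 57:171 (1:3) | 40.0 : 136.8 | 78.1% | 83.8% | 81.4% |
| 76:152 (one in three) | 53.3 : 121.6 | 84.1% | 88.4% | 86.7% |

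**5. Total needed at strict 1:3.** By the continuity-corrected method, 238 recruits give 79.9% and 240 give 80.2%. Carrying the full 14% in the intervention arm would take 4 × 62.7 = 250.8, or 252 in whole groups of four.

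**6. The fallback of 190.** Equal arms need 72 each by the same formula. 72/0.8 + 72 × 1.11/0.8 = 90 + 99.9 = 189.9, which gives 190. Split 95:95, with 20% loss and design effect 1.11, the effective sizes are 68.5 : 76 and power is 80.8%.

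**The case against.** The strongest reply is that little power is at risk, and perhaps none.

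- The continuity-corrected formula is inferred from the match to 44 and 132; the protocol does not name it. The primary analysis is an adjusted mixed-effects logit model, not a continuity-corrected test. At 57:171 two other standard calculations stay above 80%. This stands. An unpooled Wald approximation gives 74.0%, but it gives only 77.3% for the plan's own 44:132, so it is not the method behind the plan.
- The shortfall exists only at 1:3. At one in three the intervention arm has 76 people, more than the 63 behind the total. The fallback wording points the same way, since it equates 1:2 with balanced groups; by that notation 1:3 would mean one in three. The calculation itself, however, uses 44 and 132, which is one to three. This objection stands against any claim of lost power, but it does not rescue the stated figures: 76:152 is not 63:165 either.
- The inputs are uncertain by more than the shortfall. The protocol calls its inflation crude, and the primary outcome comes mainly from a registry, so 20% loss may be cautious. At 57:171, 16% loss already gives 80.1% by the corrected method. This stands as a limit on importance.

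A reader might infer that the trial is underpowered, or that the fallback of 190 has the same fault. The documents support neither. The first depends on one ratio and one approximation, and amounts to about 2 points. In the second, a balanced split loses nothing.

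**Conclusion.** The inconsistency is real and minor. The total of 228, the 1:3 ratio and a 14% inflation of the intervention arm cannot all hold, and reading the ratio as one in three does not reconcile them. At 1:3 the intervention arm is 57, six short of the 63 behind the total. Its effective size is 40.0 against the 44 required, and power is about 78% by the plan's apparent method. At one in three there is no shortfall.

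These figures assume 10% against 30%, 20% loss in both arms, and the stated 1.14 design effect acting on the intervention arm only. An unqualified statement that 228 fails to deliver 80% power would go too far. What is established is that the section reports arms, a ratio and a total that do not belong together.

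**What to change.** First reconcile 1:3 (Sample size {14}, Who will be blinded {17a}) with one in three (Abstract, Trial design {8}, consent {26a}, Participant timeline {13}), and state the chosen target ratio under Sequence generation {16a}.

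Then restate Sample size {14} with the arms that 228 yields at that ratio and the matching power, naming the formula:
- at 1:3: 57 intervention and 171 control, about 78% by the continuity-corrected method;
- at one in three: 76 and 152, about 84%.

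An allocation weight chosen to force 63:165 should not be the default. If one in three is the intended ratio, that weight would cut the intervention arm from 76 to 63 and lower power from 84.1% to 80.5%.

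The cost is a change of wording and figures, with no extra participants. If 1:3 is kept, the stated power becomes about 2 points less favourable.

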It is not clear how to best help unemployed people with persistent pain return to work (RTW). In Norway, usual care for people with persistent pain is interdisciplinary, featuring pain management services supported by physicians, psychologists, physiotherapists, and nurses [10]. Employment services in Norway take an individualised approach, often including assessments of work ability, training, and vocational rehabilitation programmes involving traineeships in sheltered businesses [11]. However, these services are not specifically tailored for people with pain. Effective vocational rehabilitation requires a combination of work-focused healthcare and supportive workplaces; unfortunately, the two are generally not coordinated [12]. Without intervention, return to work is unlikely after 2 years of unemployment [13]. Return to work rates for traditional vocational rehabilitation in the unemployed (rather than sick-listed) pain population are unclear. In 2020, we described the results of a feasibility study, done in the English Midlands, of an adapted supported work placement intervention, which featured work placement provision with case management support [13]. In this study, case managers were trained to act as a bridge between systems and institutions (e.g. between health care providers and the workplace), engage people about obstacles to work, and collaboratively agree on a return-to-work plan. We also provided supportive work placements. The developed intervention was acceptable and valued by the people involved, with around 20% of the sample obtaining paid employment within the short 6-month follow-up. The study suggested that self-perception of satisfactory functioning in role as well as management of identified obstacles may be key to increasing confidence for this group. As the study focused on feasibility, the effectiveness and cost-effectiveness of the intervention are still unknown.

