### Who will take informed consent? {26a}

We will use online and offline recruitment channels (see SPIRIT item 15 for further details). Participants will be given a participant information leaflet describing essential information about the study. Potential participants will reply to an ‘expression of interest’ form, including self-reporting of eligibility. Additionally, contact information for the research team will be provided within the participant information leaflet and expression of interest, encouraging to make contact if they have questions. Based on preferences, the consent form will be delivered by post or through Nettskjema (UiO, Oslo) for those engaging online. Before providing consent, potential participants must confirm that they have read and understood the participant information leaflet. After receiving the consent form, a trial working group member will phone participants to confirm eligibility before inviting the participant to complete a baseline questionnaire. After completing the baseline questionnaire, one-in-three people will be randomly selected to be offered the intervention. The initial cohort study consent form will request consent to be approached for the intervention. A member from the trial working group will contact those selected by phone, providing information and to ask if they have any questions and if they might like to participate. An email or post package, based on their previous preferences, will be sent to those interested after the call, and contain a participant information leaflet describing the intervention and a consent form. If there is no response to the phone call, the email or post package will note that a member from the trial working group will contact by phone to ask if the participant has any questions or requires further information. The participant information materials and informed consent form are available from the corresponding author on request.

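### The 80% power holds only if the 20-point difference already averages over people who decline the offer, which the protocol does not say, and the fallback to 190 re-uses that difference when acceptance is low

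*Protocol article*

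**What the plan says.** Trial design {8} and the consent section {26a} put randomisation after baseline and before the offer; consent to the intervention is sought only from those selected. The primary analysis is intention-to-treat (Statistical methods {20a}), with a complier average causal effect analysis as an addition ({20b}).

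Sample size {14} is based on "detecting a difference of 20% between the intervention group and the remaining cohort achieving a sustained return to work (1:3 allocation ratio"). The control rate comes from the words "Assuming a cohort return to work rate as high as 10" per cent, so the intervention-arm rate is 30%. The calculation is made "with a power of 80% and a 5% significance level", and {20a} adds "All tests will be two-sided". This gives 176 evaluable participants (132 + 44). Two allowances are then made, 20% loss to follow-up and a design effect of 1.14 in the intervention group, which lead to 228. There is none for refusal of the offer.

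The same paragraph gives a fallback. If too few people come through to form the small preparation groups, "due to the proportion of people not accepting the intervention being high, we may switch to target overall balanced randomisation (1:2"). Then "our overall required sample size will be reduced to 190 in total, with the above inflations", with unchanged assumptions apart from a design effect of 1.11.

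**The concern.** In a design that randomises to an offer, everyone who declines is still compared as part of the intervention arm. If the offer does nothing for decliners, the arm-level difference is the difference in accepters multiplied by the acceptance proportion. A sample size that states one difference without saying whether it is before or after this dilution leaves the meaning of its 80% open.

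The fallback makes the gap concrete. It comes into play when acceptance is low, which is when the arm-level difference would shrink, yet the new target is derived from the same 20 points. At stake is how a null primary result would be read: it might reflect an ineffective intervention or simply many refusals, and the stated power would not help to separate the two.

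**Working it through.** **Inputs.** From {14}: control 10%, difference 20 points, two-sided 5%, power 80%, loss 20%, design effect 1.14 (1:3) or 1.11 (fallback). The documents give no acceptance rate, so acceptance *a* is an assumption, shown over a range.

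**1. Reproduce the plan.** With k controls per intervention participant, p1 = 0.30, p2 = 0.10, p̄ = (p1 + k·p2)/(1 + k) and Δ = 0.20:

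n = {1.96·√[(1 + 1/k)·p̄(1 − p̄)] + 0.842·√[p1(1 − p1) + p2(1 − p2)/k]}² / Δ²

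n(corrected) = (n/4)·{1 + √[1 + 2(k + 1)/(n·k·Δ)]}²

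- k = 3: n = 37.2, corrected 43.7, so 44 + 132 = 176. Recruitment: (44 × 1.14 + 132)/0.8 = 227.7, so 228.
- k = 1: n = 61.6, corrected 71.3, so 72 + 72 = 144. Recruitment: (72 × 1.11 + 72)/0.8 = 189.9, so 190.

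All three stated figures reproduce. The plan therefore used a continuity correction, and its 1:2 means one in two offered.

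**2. Effective sizes** (after loss, intervention arm divided by the design effect):

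- 228 at 1:3: 171 × 0.8 ≈ 137 controls; 57 × 0.8/1.14 = 40 intervention.
- 190 balanced: 95 × 0.8 = 76 controls; 76/1.11 ≈ 68 intervention.
- 228 balanced: 114 × 0.8 ≈ 91 controls; 91.2/1.11 ≈ 82 intervention.

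**3. Dilution.** Assume 20 points in accepters and 10% in decliners. The intervention-arm rate is then 0.10 + 0.20·*a*: 30%, 25%, 22% and 20% at 100%, 75%, 60% and 50% acceptance. Power is by exact enumeration of the pooled chi-squared test, continuity-corrected/uncorrected:

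| Acceptance | 228 at 1:3 | 190 balanced | 228 balanced |
|---|---|---|---|
| 100% | 79/85% | | |
| 75% | 58/66% | | |
| 60% | 42/51% | 41/52% | 51/58% |
| 50% | 32/41% | 30/40% | 38/46% |

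At 60% and 50% acceptance, moving from 228 at 1:3 to 190 balanced changes power by +1 to −2 points. Keeping 228 under balance gains 6 to 10 points over 190.

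**4. Size needed for 80%** on the diluted difference (formulas of step 1, same inflations), 1:3 then balanced: 325 and 270 at 80% acceptance; 523 and 428 at 60%; 713 and 578 at 50%.

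**5. The other reading.** If 20 points is the difference over everyone offered, accepters must gain 20/*a* points: 25 at 80% acceptance, 33 at 60% (a rate of 43%), 40 at 50% (a rate of 50%).

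**6. Sensitivity of step 3, 228 at 1:3.** With no loss, 60% acceptance gives 50/60%. With a 5% control rate, 75% acceptance gives 74/80% and 60% gives 58/66%.

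**7. Changing the ratio mid-trial.** Illustration with assumed numbers: 33 of the first 100 are offered, then 62 of the next 90, so 95 are offered and 95 not. Of the offered, 62/95 joined after the switch; of the rest, 28/95. If return to work drifts by 8 points between the periods, the unadjusted bias is 8 × (62 − 28)/95 = 2.9 points.

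**The case against.** The strongest reply is that {14} defines the difference as one between the intervention group and the remaining cohort, which in this design is the randomised contrast. On that reading 20 points is already the intention-to-treat difference and 80% is correct. This stands as a possible reading, so the documents do not support a claim that the stated power is simply wrong. The text does not confirm it, however, and it does not explain why the same 20 points should survive a switch prompted by low acceptance.

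A reader might also infer that cutting 228 to 190 is what destroys the power. It does not: the lower number is the ordinary efficiency of balanced allocation, and step 3 shows a cost of at most about 2 points. The switch is also optional, and its stated purpose is throughput for the group sessions.

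A reader might take the feasibility result, "with around 20% of the sample obtaining paid employment within the short 6-month follow-up", as proof that 30% is out of reach. That figure comes from a shorter follow-up in another country and is not a ceiling for a 12-month endpoint.

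The assumptions in step 3 lean towards the pessimistic side. The 10% control rate is described as a high value, the registry outcome may suffer less loss than 20%, and the planned model is a mixed logistic regression rather than a corrected chi-squared test. Step 6 shows that these soften the loss without removing it.

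The complier analysis and the study of reasons for declining would help to interpret a null result, but they do not restore power for the primary comparison. Nor would restricting randomisation to those who agree to be contacted: "The initial cohort study consent form will request consent to be approached for the intervention" already covers that step, and agreeing to be approached does not prevent a later refusal.

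**Conclusion.** The point holds as a should-fix. The sample-size arithmetic is correct. What is missing is a statement that the 20 points is the average over everyone offered, and of the acceptance that this presumes. The fallback then carries the unchanged 20 points into a situation defined by low acceptance.

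If the 20 points belongs to accepters and decliners stay at 10%, power at 228 and 1:3 falls from about 79/85% at full acceptance to 32/41% at 50%. With no acceptance rate in the documents this is a range, not an estimate. The fault in the fallback is the re-used effect and the gain from balance that is given up, not the smaller number in itself. Keeping 228 under balance helps but does not bring power back to 80% at 60% or 50% acceptance.

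**What to change.** 1. In Sample size {14}, state that 20 points is the intention-to-treat difference over everyone offered and name the acceptance it presumes. Restate the power as conditional on acceptance, with a short table over a plausible range.
2. If the ratio is switched because acceptance is low, do not lower the target to 190 on the unchanged 20 points. Keep the planned 228 and report the power it gives at the acceptance observed.
3. If the ratio changes mid-trial, add pre-switch versus post-switch period to the models in {20a}, because the chance of being offered the intervention then varies with calendar time.

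The cost is a less favourable power statement, recruitment to the already planned 228 instead of 190 after a switch, and one extra covariate.
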